#### Demographic information

The following information will be collected at the initial assessment and analyzed as potential covariates and predictors of response: age, sex, work status prior to symptom onset, length of time since symptom onset in months, diagnosis provided by a medical professional as reported by the patient, medication use, previous treatment received and expectations for recovery. Expectations for recovery will be assessed with two questions: i) Do you think your pain will improve? and ii) Do you think your functional abilities will improve?

#### Psychophysical measures

Two psychophysical measures will be performed in order to estimate sensitivity of the nervous system both locally (at the point identified as “most tender”) and at two standardized locations (the area of skin over the muscle belly of the upper fibers of the trapezius and tibialis anterior).

#### Pressure pain threshold

Pressure pain threshold will be measured using a handheld digital algometer (The Wagner FDX-25; Wagner Instruments, Greenwich, CT), which has been previously demonstrated to be reliable [26, 73]. The algometers will be calibrated using a known-weight technique prior to commencing the study. The algometer will be pressed perpendicularly into the skin at a rate of approximately 50 kPa/s (5 N/s). The tester will be trained to ensure ability to apply pressure consistently at this rate. Three measurements of the pressure pain threshold will be recorded for each site and on each side of the body. The pressure pain threshold will be determined using the following standardized instructions, used in a previous study investigating pressure pain threshold [74]: “I’m going to begin applying pressure to your skin. I want you to tell me the moment the sensation changes from comfortable pressure to slightly unpleasant pain.” For consistencym the more tender side will be tested first followed by the less tender side at the “most tender” location. At the standardized locations, the right side will be tested first, followed by the left.

#### Cold hyperalgesia testing

Cold hyperalgesia will be tested using a novel test. This device consists of a Peltier Cooler used to cool 2 pairs of cylinders. The two pairs of cylinders are made of acrylic and copper. When the temperature of the cooler is 0 degrees, the cylinders of different materials will feel similar to different temperatures on the skin. The acrylic cylinder will feel like 18 degrees, and the copper will feel like 0 degrees. Each of the two cylinders will be placed in contact with the skin at the three locations in the same randomized order as was used for pressure pain threshold. The order of the two materials will also be randomized with each of the two materials being placed on the skin three times on each side. The participant will be asked to rate how cold the cylinder is on a 21 point scale (0 is unable to detect the temperature, 10 is cold but not painful, 11 is cold and slightly uncomfortable, and 20 is unbearable pain).

#### Adverse events or harms

Participants will be asked by the physiotherapist at each visit about adverse events that the patient associates with treatment. Any adverse events requiring medical care beyond the scope of the treating physiotherapist will be referred immediately.

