## Methods/Design

### Study design

This study is a randomized trial with two parallel groups. Participants will be allocated in a 1:1 ratio to treatment and wait-list groups. After the 18-week assessment (after the 6-week treatment period and the 12-week follow-up), the group initially receiving COMMENCE will receive no treatment, and the group initially on the wait-list will receive COMMENCE for 6 weeks. Both will be assessed again at 25 and 36 weeks from the baseline (1 and 12 weeks after the wait-list group finishes treatment) (See Fig. 1 for study flow). During the treatment, wait-list or follow-up periods, participants can continue with usual care with their family physician.

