**Fig. 1 Fig1:**
[figure not shown]
Study flow diagram

Between-group comparisons (objectives 1 and 2) will be limited to the 0- to 18-week period prior to the wait-list group receiving treatment. However, an 18- to 36-week period was added for ethical reasons (that is, the wait-list group will receive the treatment) and to allow four additional analyses to address objectives 3 to 6.

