### Intervention/treatment

COMMENCE consists of two visits with a physiotherapist per week over 6 weeks. One of the two visits is in a group setting, where the emphasis is on pain science education and self-management strategies using cognitive behavioral principles to support behavior change. The second visit is an individualized, one-to-one session focused on providing support to implement self-management strategies and develop an individualized, goal-oriented exercise program. Both the individual sessions and the group sessions will be carried out by a single physiotherapist (JM) for all participants.

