### Wait-list control

The wait-list control will be waiting to participate in COMMENCE after the 18-week assessment, and participants will be free to continue with “usual care.” This includes continued use of prescribed medications and recommendations from other healthcare providers. The wait-list comparison was chosen rather than a more robust comparator due to previous evidence, suggesting no difference in function when comparing other self-management programs to no-treatment or usual-care control groups.

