#### Timeline for assessments

Assessments will take place at baseline, 7 weeks (1-week follow-up), 18 weeks (12-week follow-up), 25 weeks (1-week follow-up after wait-list group treatment period) and 36 weeks (12-week follow-up after wait-list group treatment period). See Fig. 1 for the flow diagram. Demographic information will be collected at the baseline assessment. Self-reported outcome measures will be collected at all assessment time-points. The two objective tests will be collected at baseline, 18 weeks and 36 weeks.

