### Data monitoring and auditing

This trial will not have a data monitoring committee and will not include auditing of the study conduct outside of the study investigators. This decision was made because of an estimated low risk to participants. Participants with chronic pain will be medically stable and are not expected to be at a high risk of mortality. In addition, self-management programs, exercise, and pain education have all been studied with no serious adverse events reported, so no harm to patients is expected with this intervention. There are no stop rules or preliminary analyses planned.

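### Adverse events are recorded only if the patient links them to treatment, so discrete harms cannot be compared like for like between arms in weeks 0 to 18

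*Protocol article*

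**What the plan says.** The section on adverse events or harms has two sentences. The first sets the question: "Participants will be asked by the physiotherapist at each visit about adverse events that the patient associates with treatment". The second is a referral rule, "Any adverse events requiring medical care beyond the scope of the treating physiotherapist will be referred immediately", and adds no recording. The article describes no other collection of adverse events and no separate procedure for the wait-list arm.

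Three other parts of the article determine what that rule can yield:

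- **Contacts.** The Intervention/treatment section states: "COMMENCE consists of two visits with a physiotherapist per week over 6 weeks". One physiotherapist delivers all sessions. According to the Discussion, this person is also the principal investigator and attends the assessments.
- **Control arm.** The Wait-list control section states: "The wait-list control will be waiting to participate in COMMENCE after the 18-week assessment". Usual care continues meanwhile.
- **Comparison window.** The text under Fig. 1 says that between-group comparisons "will be limited to the 0- to 18-week period prior to the wait-list group receiving treatment".

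Under Timeline for assessments, both arms complete forms at 7 and 18 weeks: "Self-reported outcome measures will be collected at all assessment time-points". Under Data monitoring and auditing, the lack of a monitoring committee rests on medically stable participants and on earlier studies without serious events, "so no harm to patients is expected with this intervention".

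**The concern.** Harms in a randomised trial are best read against the control arm, because people with chronic pain have flares, falls and new problems whether or not they are treated. That requires the same question in both arms, and a question that does not ask the patient to judge cause first.

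The stated rule does neither. It filters on attribution before anything is recorded, and wait-list participants have no study treatment to attribute an event to during the comparison window. In the treated arm the patient must first decide that the programme was responsible and then say so to the person delivering it. The result is a list of suspected treatment-related events with no usable comparator.

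Two features of this trial add weight. The expectation of no harm comes from earlier studies, whereas the Participants and setting section describes a sample often left out of research, and the Discussion raises multiple morbidities and lower functional status. Also, events never asked about cannot be recovered at the analysis stage, so no later analysis plan can repair this.

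**Working it through.** The article states no figure for harms, so there is nothing to reproduce. The check has three steps: count the contacts, apply the attribution filter, and illustrate its size with assumed rates.

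**1. Contacts after baseline, weeks 0 to 18**

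| | COMMENCE | Wait-list |
|---|---|---|
| Treatment visits | 2 per week × 6 weeks = 12 | 0 |
| Assessments (weeks 7 and 18) | 2 | 2 |
| Total if assessments count as visits | 14 | 2 |

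The rule does not say whether assessments count as visits. On the narrow reading the question is put 12 times in one arm and never in the other. On the wide reading it is put 14 times against 2.

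**2. The attribution filter**

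- *Wait-list, weeks 0 to 18.* No COMMENCE has been given, so no event can be attributed to it, even on the wide reading. A participant might take the word treatment to cover usual care, which the rule does not exclude. Such a report would concern a different cause.
- *Wait-list, after week 18.* According to the Study design section, "the group initially on the wait-list will receive COMMENCE for 6 weeks". Attributed events can then arise, but from treated people outside the comparison window, so they cannot serve as control data.
- *COMMENCE.* Only attributed events are recorded. Events that treatment causes but the patient does not connect with it are lost.

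**3. Illustration (all rates assumed; the article gives none)**

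Let p be the true proportion with any event, equal in both arms, and f the share of treated participants with an event who attribute it to treatment. The arm size of 55 comes from the Sample size section.

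Expected number listed in the COMMENCE arm = 55 × p × f. The wait-list arm has 0 attributed to the study treatment. Apparent risk difference = p × f − 0; true difference = p − p = 0.

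| p (assumed) | f = 25% | f = 75% | Apparent difference |
|---|---|---|---|
| 10% | 55 × 0.10 × 0.25 = 1.4 | 55 × 0.10 × 0.75 = 4.1 | 2.5 to 7.5 points |
| 20% | 55 × 0.20 × 0.25 = 2.8 | 55 × 0.20 × 0.75 = 8.3 | 5 to 15 points |
| 40% | 55 × 0.40 × 0.25 = 5.5 | 55 × 0.40 × 0.75 = 16.5 | 10 to 30 points |

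The error can also run the other way. At p = 20%, 55 × 0.20 = 11 treated participants have an event and 11 × (1 − f), that is 2.8 to 8.3 of them, go unrecorded. Any of these that treatment caused is a missed harm.

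**The case against.** The strongest reply is that nothing planned is broken. Between-group comparison belongs to objectives 1 and 2, which cover function and the listed secondary outcomes. Harms are not among them. The rule describes surveillance for treatment-related events with a referral step, and for that limited purpose it is serviceable. This stands: a reader might infer a contradiction or a failed analysis, and the article supports neither.

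A reader might also infer that the wait-list arm records zero events by construction. That is too strong. The Participant retention section uses the word visit for assessments as well, the physiotherapist is present when the forms are completed, and treatment is not defined as COMMENCE alone. Reports about usual care are possible, but they would not be comparable.

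Nor does it follow that the trial cannot detect worsening. Pain intensity, pain interference, function, fatigue and depressive symptoms are self-reported at 7 and 18 weeks and compared between arms. Healthcare visits are a secondary outcome, and other treatments are recorded and compared. Sustained average worsening and extra care use are therefore partly covered. These are scores and counts, however, and do not identify a fall, an injury, a short-lived flare or a new problem.

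It is tempting, too, to say that the decision against a monitoring committee is undermined. That decision was a prospective judgement, not a hypothesis that the trial undertook to test. With 55 treated participants, even zero events leaves an upper 95% limit of about 3/55 ≈ 5%, so an added item would not settle rare serious harm either.

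Finally, this is a condensed article, and the full protocol may contain more. That limits certainty about what else is collected. It does not remove the point, because the article states what is asked and does not leave it open.

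**Conclusion.** The point holds as a design weakness in how harms are ascertained. In weeks 0 to 18, the only randomised comparison window, the wait-list arm can contribute no events attributed to the study treatment, any usual-care reports are not like for like, and unattributed events are missed in the treated arm. Discrete events therefore cannot be compared between arms, while average changes in symptoms, function and healthcare use can.

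The size is unknown, since the article gives no event rate or attribution share. Under the assumed ranges above, the listing could show an apparent excess of 2.5 to 30 percentage points with no true difference. That figure matters only if someone reads the treatment-related listing as a controlled comparison, which the protocol does not propose.

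The conclusion rests on the harms section being the whole of the collection procedure. If the full protocol already puts an attribution-free question to both arms, the point falls away. The primary analysis and the sample size are unaffected. The change is worth making because it is cheap and the information cannot be recovered later.

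**What to change.** Add one identical item to the self-report forms of both arms at 7 and 18 weeks, asking about any new or worsened health problem, fall or unplanned care since the last assessment, whether or not the participant links it to treatment. The recall periods are then 7 weeks and 11 weeks (18 − 7), the same in both arms. Report the counts descriptively by arm, with the number who answered the item as denominator. Keep the physiotherapist's visit-level question as a separate listing of treatment-related events, and do not set that listing against the wait-list arm.

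The cost is one form item and one descriptive table. Under Protocol modifications, the change also needs written notice to the investigators and the ethics board and an update of the registry. Recruitment began in September 2013 and was continuing at submission, so participants assessed before the change will lack the item. The report should give the date of introduction and the number asked in each arm. Answers will still be unblinded self-report, a limit that the Discussion already acknowledges for the other self-report measures.

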#### Treatment adherence

Treatment adherence will be assessed through a combination of attendance (categorized as < 25 %, 25 to 49 %, 50 to 74 %, or ≥ 75 % of visits) and adherence to self-management strategies. Adherence to recommended self-management strategies will be described as either completed or not completed by the clinician when reviewing the participant workbook at the individual treatment session.

#### Timeline for assessments

Assessments will take place at baseline, 7 weeks (1-week follow-up), 18 weeks (12-week follow-up), 25 weeks (1-week follow-up after wait-list group treatment period) and 36 weeks (12-week follow-up after wait-list group treatment period). See Fig. 1 for the flow diagram. Demographic information will be collected at the baseline assessment. Self-reported outcome measures will be collected at all assessment time-points. The two objective tests will be collected at baseline, 18 weeks and 36 weeks.

### Participant retention

Participant retention will be encouraged by clearly asking only those willing to commit to all assessment and treatment time points to enroll in the study. In addition, free parking is provided for all treatment and assessment visits, treatment is provided free-of-charge, and a small gift card ($20) is provided at each assessment time point to thank participants and encourage patient follow-up.

### Data collection and management

Hard copies of self-report data will be collected directly for the outcome measures previously listed and referenced. The measures will be completed at WACHC, with the treating physiotherapist and a research assistant present. Demographic data will be collected on pre-piloted study forms. Data will be transferred directly to a database by a trained research assistant or study investigator. Data quality will be assured through checking 10 % of the data entered. The data will be collected and stored using only participant codes with no patient identifiers. Hard copies of forms will be stored in a locked cabinet within a locked office at WACHC. The electronic database will be password protected and stored on a password protected computer. Only study investigators or staff will have access to the data.

### Data monitoring and auditing

This trial will not have a data monitoring committee and will not include auditing of the study conduct outside of the study investigators. This decision was made because of an estimated low risk to participants. Participants with chronic pain will be medically stable and are not expected to be at a high risk of mortality. In addition, self-management programs, exercise, and pain education have all been studied with no serious adverse events reported, so no harm to patients is expected with this intervention. There are no stop rules or preliminary analyses planned.

### Analysis

Statistical analysis will be conducted using Stata software, version 13 (StataCorp, College Station, TX, USA). Baseline characteristics for both treatment and wait-list groups will be presented as means and standard deviations for normal data, and medians and interquartile range for non-normal data, and number of patients and percentages for categorical data. Between-group comparisons will be made for baseline data using a Student’s *t*-test for continuous data and Chi squared or Fisher’s exact test for categorical variables to determine the results of the randomized allocation.

To address objectives #1 and 2, between-group differences in change in primary (SMFA-DI) and secondary outcomes will be analyzed using linear mixed-effects modelling with repeated measures at 0, 7, and 18 weeks. A *P* value of less than 0.05 will be considered indicative of statistical significance for all comparisons. The minimum changes required for the change to be considered clinically meaningful for each scale are listed in Table 1. An advantage of using linear mixed-effects modelling is the ability to utilize all available data points without multiple imputation when there are multiple missing data points [75]. Between-group comparisons will be limited to data collected before the 18-week assessment time point due to anticipated carry over effects due to the long-term changes in function associated with exercise approaches for people with chronic pain [19, 20]. Analysis will use intention-to-treat principles.

To address objective #3, a within-group analysis in the wait-list group will be performed comparing the change in function during the treatment period (weeks 18 to 36) to the change in function during the wait-list period (weeks 0 to 18) using a mixed effects model. If there is no change during the wait-list period, this analysis allows for a secondary estimate of treatment effect similar to a diamond response design [76]. Goldsmith et al. suggest that if the magnitude of the effect of the intervention is similar to that estimated through the comparison between groups during the 0 to 7 week period, then they may be pooled for a more precise estimate of treatment effect [76].

To address objective #4 and estimate whether treatment effects are maintained beyond the 18-week assessment, the functional score (SMFA-DI) at the end of treatment (7 weeks) will be compared with the functional score at the 25- and 36-week assessments using a linear mixed effects model.

To address objective #5, the influence of the 18-week delay on the treatment effect will be determined by comparing the magnitude of treatment effect from the waist list group (from objective #3) with the estimate of the magnitude of treatment effect from the treatment group (from objective #1).

In order to address objective #6, each of the patient demographics, outcome measure scores, and objective measures will be tested for univariate relationship with SMFA-DI change score at 18 weeks (difference between SMFA-DI at 18 weeks and SMFA-DI at baseline) using a Pearson r for continuous variables and Chi squared tests for categorical variables. Variables with a significance of <0.10 will be included in the multivariate analysis so that no potential predictive variables will be overlooked. Potential predictor variables will be entered into a series of multiple regression models to determine which combination of baseline variables best predict changes in SMFA-DI.

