### Sample size

The sample size necessary for a randomized controlled trial with three repeated measures at 0, 7 and 18 weeks was calculated using online sample size software (GLIMMPSE 2.0) using methods detailed by Muller et al. [37–39]. The calculation was performed using a significance level of 0.05, a power of 0.8, a minimum detectable mean difference between groups of 10 points on the Short Musculoskeletal Function Assessment Dysfunction Index (SMFA-DI) [40] at both 7 weeks and 18 weeks, and a standard deviation at each time-point of 23 points on the SMFA-DI based on baseline data from a series of 20 people with chronic pain referred to physiotherapy at WACHC. The calculations were made assuming a correlation between baseline and 7 weeks of 0.84, a correlation between baseline and 12 weeks of 0.82, and a correlation between 7 weeks and 18 weeks of 0.84, based on the same clinical population. The needed sample size calculated was 88 participants. To account for a potential 20 % drop-out rate, the investigators will recruit 110 participants (n = 55 in each group).

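### The planned contrast in change states neither a common baseline mean nor baseline adjustment; if the arms' baseline means are free, it gives up a modest amount of precision that one sentence would recover

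*Protocol article*

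**What the plan says.** For objectives 1 and 2 the Analysis section says that "between-group differences in change in primary (SMFA-DI) and secondary outcomes will be analyzed using linear mixed-effects modelling", and gives the model as "linear mixed-effects modelling with repeated measures at 0, 7, and 18 weeks". Baseline is therefore part of the outcome vector. The section does not list the fixed effects and does not say whether the two arms share a baseline mean.

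Three other places bear on how to read this:

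- The Analysis section also plans significance tests of baseline differences between the arms, and gives them no role in the effect estimate.
- The Demographic information section lists items that may serve as covariates. The baseline score of the outcome is not on that list.
- The Outcomes section uses baseline outcome scores only as candidate predictors of response.

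The Sample size section supplies what is needed to size the effect: "a significance level of 0.05, a power of 0.8", "a minimum detectable mean difference between groups of 10 points", "a standard deviation at each time-point of 23 points on the SMFA-DI", and "The calculations were made assuming a correlation between baseline and 7 weeks of 0.84", followed by 0.82 between baseline and the later visit and 0.84 between weeks 7 and 18.

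**The concern.** Baseline is measured before allocation is revealed, so the arms have the same expected baseline mean. A model that gives each arm its own baseline mean spends information on estimating a difference known to be zero in expectation, then subtracts that noisy estimate in full from the follow-up difference. Having week 0 in the outcome vector does not by itself yield the gain of an analysis of covariance. The gain comes only if the baseline means are held equal or baseline enters as a covariate.

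What is at stake is precision: wider intervals than the collected data allow, for the primary outcome and for every continuous secondary outcome analysed the same way. The loss grows as the correlation with baseline falls. The trial was sized on SMFA-DI alone, so the secondary outcomes are where precision is least assured.

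**Working it through.** **Inputs (Sample size section).** SD 23 at each visit; difference 10 points; alpha 0.05, taken as two-sided because sidedness is not stated; 88 evaluable participants, so 44 per arm under 1:1 allocation; correlation with baseline 0.84 at week 7 and 0.82 at the last visit. The text attaches 0.82 to 12 weeks; I take it as the 18-week visit.

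**The plan's own figure.** The dropout step reproduces: 88 / 0.8 = 110. The 88 itself does not follow at 80% power from the stated inputs. A change-score comparison at week 18 needs 60 in total by normal approximation (62 by t-test), and the joint group-by-time test needs 56. At 88 the joint test has about 95% power. That is a separate matter; I use 88 below only as the plan's evaluable number.

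**The two contrasts.** Let D0 and Dt be the arm differences in observed means at week 0 and week t, with n per arm, SD σ and correlation ρ. With complete data:

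- Free baseline means: estimate = Dt − D0, variance = (2σ²/n) × 2(1 − ρ).
- Common baseline mean, or baseline as covariate: estimate = Dt − ρD0, variance = (2σ²/n) × (1 − ρ²).
- Ratio, adjusted to change: (1 − ρ²) / [2(1 − ρ)] = (1 + ρ)/2.

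A generalised least squares calculation for the three-visit model, with and without the baseline constraint, returns the same ratios.

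**Primary outcome, 44 per arm.** SE = SD × √(2/44) = SD × 0.2132. Power = Φ(10/SE − 1.96).

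| | Week 7, change | Week 7, adjusted | Week 18, change | Week 18, adjusted |
|---|---|---|---|---|
| Variance factor | 0.32 | 0.2944 | 0.36 | 0.3276 |
| SD | 13.01 | 12.48 | 13.80 | 13.16 |
| SE | 2.77 | 2.66 | 2.94 | 2.81 |
| 95% CI half-width | 5.44 | 5.21 | 5.77 | 5.50 |
| Power | 95.0% | 96.4% | 92.5% | 94.6% |

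Variance ratios: 0.2944/0.32 = 0.92 and 0.3276/0.36 = 0.91. The gain matches that from 1/0.92 − 1 = 9% more participants at week 7 and 1/0.91 − 1 = 10% more at week 18.

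**With dropout.** For 110 randomised and an assumed loss of 10% by week 7 and 20% by week 18, the variance ratios are 0.927 and 0.925. The week-18 SE goes from 2.88 to 2.77 and power from 93.5% to 95.1%.

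**Continuous secondary outcomes.** Their correlations are not given. Over an assumed range:

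| Assumed ρ | (1 + ρ)/2 | Variance reduction |
|---|---|---|
| 0.4 | 0.70 | 30% |
| 0.5 | 0.75 | 25% |
| 0.6 | 0.80 | 20% |
| 0.7 | 0.85 | 15% |

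**The same loss seen through chance imbalance.** The two contrasts differ by (1 − ρ)D0. At 44 per arm the SE of D0 is 23 × 0.2132 = 4.90 points, so an imbalance of one SE moves the week-18 change contrast by 0.18 × 4.90 = 0.88 points relative to the adjusted one. This restates the variance difference; it is not a second harm.

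**The case against.** The strongest objection is that free baseline means are nowhere stated. A mixed model with week 0 as an outcome and a common baseline mean fits the same sentence, and the parametrisation of a mixed model is the kind of detail that a condensed article may leave to an analysis plan not seen here. This stands in part. A reader might infer that the protocol commits to separate baseline means; it does not, and the point has to be conditional. It survives because the stated target is a difference in change, the common-baseline constraint is a deliberate choice that nothing mentions, and the baseline score is absent from the listed covariates. The free reading is the natural one, and the remedy names a better method rather than asking for missing detail.

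Three stronger inferences are tempting and not supported:

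- *That the planned estimate is biased.* It is unbiased under randomisation. The issue is efficiency.
- *That the primary comparison is underpowered.* On the plan's inputs, power exceeds 80% under either analysis, and adjustment adds about two percentage points at week 18.
- *That the secondary analyses lose a known 15% to 25% or more.* Those figures rest wholly on assumed correlations.

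Also, (1 + ρ)/2 does not carry over directly to work status, which is categorical.

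**Conclusion.** The point holds conditionally, as a modest efficiency gain. If the arms' baseline means are free, the planned contrast has a standard error 4% to 5% larger for SMFA-DI than a baseline-adjusted contrast needs to have. That amounts to 0.27 points of week-18 confidence-interval half-width (5.77 against 5.50), on an outcome whose important difference is set at 10 points. For continuous secondary outcomes the loss is larger wherever the baseline correlation is lower, by an amount the protocol does not allow anyone to compute.

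The figures rest on the planning SD and correlations, equal variances across visits, 0.82 belonging to week 18, a two-sided 0.05 level and complete data at 44 per arm. With the assumed dropout the variance reduction is 7% to 8%. If the full analysis plan already imposes a common baseline mean, there is no loss and the sentence below merely records it.

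**What to change.** Add one sentence to the Analysis section: for SMFA-DI and the continuous secondary outcomes, the mixed model for weeks 0, 7 and 18 constrains the two arms to a common baseline mean, with group entering only through group-by-week-7 and group-by-week-18 terms. This keeps week 0 as an outcome and uses all available data, which the protocol names as its reason for choosing a mixed model.

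Modelling weeks 7 and 18 as outcomes, with baseline by visit as covariate, is a close alternative. It coincides with the constrained model when data are complete, but it drops participants who have only a baseline value. That makes it the second choice in a trial planning for 20% dropout.

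The cost is the sentence and at most about one degree of freedom. No further data, participants or visits are needed. Work status is not covered by this change. The wording should be fixed before the data are analysed, since free, constrained and covariate-adjusted models can give different primary estimates.
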